## Abstract

**Background:**

Idiopathic macular holes are an important cause of blindness. They have an annual incidence of 8 per 100,000 individuals, and prevalence of 0.2 to 3.3 per 1000 individuals with visual impairment. The condition occurs more frequently in adults aged 75 years or older. Macular holes can be repaired by surgery in which the causative tractional forces in the eye are released and a temporary bubble of gas is injected. To promote successful hole closure individuals may be advised to maintain a face-down position for up to 10 days following surgery. The aim of this study is to determine whether advice to position face-down improves the surgical success rate of closure of large (>400 μm) macular holes, and thereby reduces the need for further surgery.

**Methods/Design:**

This will be a multicentre interventional, comparative randomised controlled clinical trial comparing face-down positioning with face-forward positioning.

At the conclusion of standardised surgery across all sites, participants still eligible for inclusion will be allocated randomly 1:1 to 1 of the 2 treatment arms stratified by site, using random permuted blocks of size 4 or 6 in equal proportions. We will recruit 192 participants having surgery for large macular holes (>400 μm); 96 in each of the 2 arms of the study. The primary objective is to determine the impact of face-down positioning on the likelihood of closure of large (≥400 μm) full-thickness macular holes following surgery.

**Discussion:**

This will be the first multicentre randomised control trial to investigate the value of face-down positioning following macular hole standardised surgery.

**Trial registration:**

UK CRN: 17966 (date of registration 26 November 2014).

**Electronic supplementary material:**

The online version of this article (doi:10.1186/s13063-015-1048-8) contains supplementary material, which is available to authorized users.

## Introduction

### Background

Idiopathic macular holes are an important cause of blindness. They have an annual incidence of 8 per 100,000 individuals [1], and a prevalence of 0.2 [2] to 3.3 [3] per 1000 individuals with visual impairment. The condition occurs more frequently in adults aged 75 years or older [2]. Macular holes can have a devastating impact on quality of life and independence but can be repaired by surgery in which the causative tractional forces in the eye are released and a temporary bubble of gas is injected. To promote successful hole closure individuals may be advised to maintain a face-down position for up to 10 days following surgery. However, face-down positioning can be arduous [4] and associated with significant adverse effects [5], and evidence of its value is lacking. A recent Cochrane review [6] highlighted the need for an appropriately designed, adequately powered randomised controlled clinical trial to determine with confidence its value. The review reported that estimated effects were in favour of positioning but differences were not statistically significant for smaller macular holes. It concluded that face-down positioning may improve the likelihood of successful surgery for large macular holes (400 μm or greater in diameter) and highlighted the need for an appropriately designed, adequately powered randomised controlled clinical trial to determine with confidence the value of advice to position face-down.

### Rationale

The benefit of face-down positioning to the success of surgery is unproven; evidence to guide individuals on its impact is lacking and advice offered by clinicians varies widely. The current lack of evidence with which to guide patients has led to a lack of consensus among clinicians and wide variation in clinical practice.

To address the limitations in the evidence we will perform a trial to determine whether advice to position face-down, as opposed to face-forward, improves the probability of macular hole closure at 3 months after surgery, and so reduces the need for further surgery. We will test whether advice to position face-down results in a better outcome than an inactive face-forward position following surgery for large macular holes (≥400 μm).

A previous pilot randomised controlled trial (RCT) [7] has demonstrated the feasibility of this definitive RCT.

We have chosen to include only large macular holes (≥400 μm) because the available evidence suggests that face-down positioning is of more relevance to larger holes than for smaller macular holes [7–9]. In addition, the role of surgery in the management of smaller macular holes may be influenced in the future by the introduction of enzymatic vitreolysis techniques; intra-ocular injection of ocriplasmin can help induce closure in up to 40 % of smaller macular holes [10]. However, this approach is not designed for larger holes, the management of which is likely to involve surgery for the foreseeable future.

The proposed trial has been designed taking into account the views of individuals with macular holes and clinicians. The pilot study suggested a benefit of positioning following surgery for large macular holes. Previous pilot study subjects were invited to form a Patient Advisory Panel to advise on the design and methodology of this new RCT. Both patients and clinicians indicated that randomisation to either face-down positioning for as long as 10 days, or conversely to no positioning at all, would adversely affect recruitment to the trial because these alternatives are typically considered too arduous or would present too high a risk of non-closure, respectively. Instead, we have reached a consensus, based on the approach used by Guillaubey et al [8], on the alternatives of 5 days positioning either face-down or in an inactive face-forward position.

For the primary outcome we have chosen successful closure of the macular hole because, according to our Patient Advisory Panel, this is directly relevant to patients; hole closure is essential for a favourable impact on sight and determines whether further surgery is required. Although visual acuity is a relevant measure of functional outcome, its validity is limited to some extent in the short term by the confounding influence of secondary lens opacity and does not directly determine the need for further surgery.

We have chosen not to attempt to measure objectively the compliance of subjects with positioning. This is because self-reported compliance is of unknown reliability, and objective monitoring risks influencing behaviour artificially and unpredictably. Instead, we have taken the pragmatic approach to determine the value of the *advice* to patients regarding position. However, following the period of positioning we will ask subjects to say retrospectively how easy they found it to maintain their allocated position (on a scale of 0 (very difficult) to 10 (very easy). We will also assess their quality of life using the National Eye Institute Visual Function Questionnaire (VFQ-25).

The trial will benefit patients by providing reliable information on the value of positioning following surgery for large macular holes, thereby enabling them to make an appropriately informed choice about the management of their condition.

The research will benefit the National Health Service (NHS) because by determining the value of face-down positioning we can expect to improve the likelihood of prompt successful surgery and hence reduce the amount of additional resource required for further clinical management and associated costs.

### Objectives

The aim is to determine whether advice to position face-down improves the surgical success rate of closure of large (≥400 μm) macular holes, and thereby reduces the need for further surgery.

#### Primary objective

The primary objective is to determine the impact of face-down positioning on the likelihood of closure of large (≥400 μm) full-thickness macular holes following surgery.

#### Secondary objective

The secondary objective is to determine the impact of face-down positioning on sight, quality of life and wellbeing.

## Methods/Design

This will be a multicentre interventional, comparative randomised controlled clinical trial comparing face-down positioning with face-forward positioning.

We will recruit 192 participants having surgery for large macular holes (≥400 μm); 96 in each of the 2 arms of the study.

### Inclusion criteria

Presence of an idiopathic full-thickness macular hole, greater than or equal to 400 μm in diameter as measured by optical coherence tomography (OCT).Patients electing to have surgery for a macular hole, with or without simultaneous phacoemulsification and intra-ocular lens implant.Ability and willingness to position face-down or in an inactive face-forward position.

### Exclusion criteria

Age-related macular degeneration; glaucoma; diabetic retinopathy; retinal degeneration; amblyopia; previous vitrectomy surgery (refractive error, lens opacity and previous use of ocriplasmin are not exclusion criteria).Traumatic macular hole.History of visual loss suggesting macular hole duration longer than 12 months.Presence of a retinal tear identified during surgery for which postoperative positioning is advised.

## Informed consent

Eligible candidates will be approached at their baseline visit by the clinical team, provided with information about the trial and invited to participate. They will be given time to consider their decision and the opportunity to ask questions. Investigators will ensure that information about equipoise is provided impartially so as to avoid potential bias by influencing compliance with advice to position. Should candidates elect to participate, informed consent will be obtained (see Additional file 1) at the time of listing for surgery. Candidates will understand that that although consenting to participate in the trial, they will be formally enrolled only if the inclusion and exclusion criteria are still met following surgery.

We will not be recruiting/consenting subjects who we feel lack capacity.

The surgery will involve vitrectomy (using instruments of any gauge), internal limiting membrane (ILM) peeling (with or without staining by a vital dye), fluid-air exchange and injection of octafluoropropane (C3F8) 14 % gas. Vitrectomy may be combined with phacoemulsification and intra-ocular lens implant.

Subjects will be randomised immediately following surgery, unless exclusion criteria are met during surgery.

### Intervention

The intervention is advice to adopt face-down positioning (see Additional file 2): subjects will be advised to maintain a face-down position for a total of at least 8 consecutive or non- consecutive hours a day for 5 days following surgery.

The comparator is advice to adopt face-forward positioning (see Additional file 3): subjects will be advised to maintain a face-forward position, inactive, for at least 8 consecutive or non-consecutive hours a day for 5 days following surgery.

Subjects in either group will be allowed a 15-minute break (every hour) from their allocated position. In the position-free-time we will advise subjects to avoid the face-up position.

Face-down or face-forward positioning will be advised during waking hours only, not during sleep. We will advise subjects to avoid the face-up position during sleep.

Investigators will explain positioning to candidates prior to surgery, providing written instructions with diagrams.

### Randomisation

Eligible candidates will be invited to participate and to sign the consent form prior to surgery.

At the conclusion of standardised surgery across all sites, participants still eligible for inclusion will be allocated randomly 1:1 to one of the 2 treatment arms (refer to the flow diagram in Additional file 4) stratified by site, using random permuted blocks of size 4 or 6 in equal proportions.

Randomisation will be performed using a secure bespoke online randomisation service implemented by the PCTU (Pragmatic Clinical Trials Unit). Each site will be provided with a unique log-in username and password to access the service. Online randomisation will be available 24 hours a day, 7 days a week apart from short periods of scheduled maintenance. Access to the service will be restricted to staff as delegated by the Principal Investigator (PI). They will input the participant ID and details required for randomisation, and then will be presented with immediate on-screen randomisation. The randomisation system will have built-in checks to check that (1) the participant ID is not a duplicate, and (2) the date of birth is within the eligible age set in the protocol.

Once the subject has been randomised, the enrolment of this subject will be documented on the enrolment log. An Email will be automatically generated to notify the Chief Investigator’s (CIs) team and PCTU of all participants randomised to the trial.

### Masking

Subjects and clinicians will be unmasked to treatment allocation.

Investigators assessing the primary endpoint by grading of OCT scans will be masked to treatment allocation. This will be achieved by electronic capture of OCT images which are presented anonymously to the grading clinicians. Each clinician will be masked to their colleagues grading. Postoperative hole closure will be determined according to the presence (open) or absence (closed) of any gap between the opposing edges of the hole. No measurement is involved. In the event of disagreement between clinicians, the opinion of a third clinician (also masked) will be sought.

### Follow-up

Subjects will attend for follow-up assessment as part of the trial at 3 months following surgery. Their surgical teams will manage their routine postoperative clinical care in the meantime.

The primary outcome, macular hole closure, will be determined by masked assessment of OCT scans acquired at 3 months.

### Unit of analysis

All ocular assessments relate to the study eye. In the event that a subject is having surgery for bilateral macular holes (which are not operated on simultaneously), the first eye to be operated on during the trial will be the study eye.

### Data collection

Table 1 shows the schedule of assessments.

**Table 1 Tab1:** Schedule of assessments

Assessment	Preoperative	Surgery	3 months postoperative
Age	x		
Sex	x		
Ethnicity	x		
Laterality	x		
Duration of symptoms	x		
BCVA	x		x
Lens status: phakic/pseudophakic	x		x
Informed consent	x		
Surgery		x	
Randomisation		x	
Macular hole diameter on OCT	x		
Macular hole status (closed; open flat; open elevated)			x
QoL VFQ-25 questionnaire	x		x
Subject-reported experience of positioning			x
If primary repair of macular hole failed, was second operation performed/planned			x

*BCVA* best-corrected visual acuity, *OCT* optical coherence tomography, *QoL* quality of life, *VFQ-25* Visual Functional Questionnaire

Pre-operative data collection:Demographic data (age, sex, ethnicity)LateralityDuration of symptomsBest-corrected visual acuity (BCVA) measured using Snellen charts at a standard distance of 6 metresOCT with recording of minimal hole diameter (see Additional file 5)

### Outcome measures

#### Primary outcome

The primary outcome will be anatomical closure of the macular hole, determined at 3 months after surgery by masked assessment of OCT scans.

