#### Secondary outcomes

Further surgery for macular hole, performed or plannedBCVA using standard Snellen chart at 6 metresPatient-reported experience of positioning at 3 monthsPatient-reported health and quality of life as assessed at baseline and at 3 months using the National Eye Institute Visual Function Questionnaire (VFQ-25)

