### Analysis

Baseline characteristics will be tabulated in the two treatment arms.

Proportions of macular hole closures at 3 months will be compared between treatment arms using logistic regression adjusting for age and sex, with site as a random effect.

Visual acuity at 3 months will be compared using linear regression adjusting for age, sex, and baseline visual acuity, with site as a random effect. We will also adjust for surgery type in the logistic regression analysis. Questionnaire scores assessed at 3 months will be compared using linear regression adjusting for age and sex, with site as a random effect.

The numbers of participants who decline to participate, fail screening, or withdraw or are lost to follow-up will be recorded in a Consolidated Standards of Reporting Trials (CONSORT) flow-chart.

The analyses will be on an intention-to-treat basis, and every effort will be made to collect complete data. If any outcome data are missing we will analyse available subjects only (this is unbiased under a missing-at-random assumption where missingness depends only on variables adjusted for in the analysis), but we will also perform secondary analyses investigating the missing-at-random assumption and involving further baseline covariates if necessary.

OCT scans will be anonymised and sent to two independent retinal surgeons who will grade the macular hole as closed; open and flat (without a cuff of subretinal fluid), or open and elevated (with a cuff of subretinal fluid). The readers will be masked to the identity and treatment allocation of the subject. In the event of any disparity in grading, a third independent retinal surgeon, also masked to identity and treatment allocation, will arbitrate.

A formal statistical analysis plan will be signed off by the Trial Steering Committee prior to analysis.

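### The primary outcome is hole status on the 3-month OCT with no condition on further surgery, so a failed index repair closed by re-operation before that scan would be graded a success

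*Protocol article*

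**What the plan says.** - **Definition (Primary outcome).** "The primary outcome will be anatomical closure of the macular hole, determined at 3 months after surgery by masked assessment of OCT scans". Follow-up repeats the timing and source: "The primary outcome, macular hole closure, will be determined by masked assessment of OCT scans acquired at 3 months".
- **Grading (Masking).** "Postoperative hole closure will be determined according to the presence (open) or absence (closed) of any gap between the opposing edges of the hole". The readers work from anonymised images. The Analysis section adds two grades of open hole (flat or elevated) and a third reader for disagreements, but nothing about surgical history.
- **Further surgery.** At the 3-month visit Table 1 asks "If primary repair of macular hole failed, was second operation performed/planned". The Secondary outcomes list "Further surgery for macular hole, performed or" planned, separately from the primary outcome.
- **Care before 3 months (Follow-up).** "Their surgical teams will manage their routine postoperative clinical care in the meantime".
- **Who knows the allocation (Masking).** "Subjects and clinicians will be unmasked to treatment allocation". Only the OCT readers are masked.
- **Purpose.** Objectives states the aim as a higher success rate of the surgery and, through it, less need for more surgery. Rationale explains that closure was chosen partly because it decides whether another operation is needed.
- **Missing outcomes (Analysis).** "If any outcome data are missing we will analyse available subjects only", with secondary analyses that examine the missing-at-random assumption.

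**The concern.** The trial asks whether positioning advice after the index operation helps that operation to close the hole. The endpoint is a snapshot at 3 months, and the readers cannot tell from an anonymised scan whether one operation or two produced the result. A second operation inside the window can therefore turn a failure of the index repair into a primary success. The same participant could then count as a success on the primary outcome and as an event on the further-surgery secondary outcome.

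On the design assumptions, failures are four times as common face-forward (20%) as face-down (5%). Rescue by re-operation would therefore add more successes to the face-forward arm and narrow the difference that the trial is sized to find. The decision to re-operate, and its timing, also lie with clinicians who know the allocation, and masked reading of the later scan cannot correct for that.

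**Working it through.** **Inputs from the protocol article (Sample size and power calculation).** Closure 80% face-forward and 95% face-down; 86 evaluable per arm; 85% power; 10% loss; 96 recruited per arm. The significance level is not stated. I assume two-sided 5%, which reproduces the stated number.

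**Input not in the documents.** f is the fraction of index failures that are re-operated and closed before the 3-month scan. It is an assumption throughout and is shown as a range.

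**Step 1: the plan's own figure.** Pooled-variance formula for two proportions, no continuity correction:

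n = [1.960 × √(2p̄(1−p̄)) + z(power) × √(p₁(1−p₁) + p₂(1−p₂))]² / (p₂−p₁)²

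With p₁ = 0.80, p₂ = 0.95, p̄ = 0.875 and z(0.85) = 1.036, the two square roots are 0.4677 and 0.4555, and n = 85.7, so 86 per arm. Power at 86 is 85.1%, and 86/0.9 = 95.6, so 96. The sample-size statement is reproduced and is not in error.

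**Step 2: closure as the endpoint would record it.** If f is the same in both arms, recorded closure is p + f(1−p) and the difference shrinks to 0.15 × (1−f).

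**Step 3: power at 86 per arm.** Power = Φ{[(p₂−p₁)√86 − 1.960√(2p̄(1−p̄))] / √(p₁(1−p₁) + p₂(1−p₂))}, using the recorded proportions.

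| f | Face-forward | Face-down | Difference (points) | Power |
|---|---|---|---|---|
| 0 | 80.0% | 95.0% | 15.0 | 85% |
| 5% | 81.0% | 95.25% | 14.25 | 83% |
| 10% | 82.0% | 95.5% | 13.5 | 81% |
| 25% | 85.0% | 96.25% | 11.25 | 72% |
| 50% | 90.0% | 97.5% | 7.5 | 53% |

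**Step 4: the same in eyes.** Design failures are 86 × 0.20 = 17.2 and 86 × 0.05 = 4.3. At f = 10% about two eyes change grade in all (1.7 and 0.4). At f = 25% it is about four against one (4.3 and 1.1).

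**Step 5: when re-operation does not always close the hole.** f is the share re-operated times the closure rate of re-operation. With that closure rate taken as 80% to 100%, re-operating on 25% of failures gives power of 75% to 72%, and re-operating on 50% gives 61% to 53%.

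**Step 6: f differing by arm.** Take f = 40% face-forward and 20% face-down: 1 − 0.20 × 0.6 = 88% against 1 − 0.05 × 0.8 = 96%, power 49%. With the two values swapped: 1 − 0.20 × 0.8 = 84% against 1 − 0.05 × 0.6 = 97%, power 83%. If true index closure were 80% in both arms, f of 40% and 20% would record 1 − 0.20 × 0.6 = 88% and 1 − 0.20 × 0.8 = 84%, a 4-point gap with no effect of positioning. Unequal f can thus bias the comparison as well as dilute it.

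**The case against.** The strongest reply is that no sentence says a rescued eye is a success. The aims, the rationale and the Table 1 reference to failure of the primary repair all point to the index operation. A formal statistical analysis plan is promised, and this is a condensed article, so the rule may be written elsewhere. The first part is fair: the result comes from applying the definition, not from an explicit statement. But the article does state the endpoint, its timing, its source and its grading rule, and none of them carries an exception. If the index operation is what is meant, the 3-month scan cannot show its result in a re-operated eye, and no substitute is named. A plan that counted such eyes as failures would be altering the endpoint stated here.

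Three stronger readings are tempting and are not supported.

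- A reader might infer that the protocol expects early re-operation. The form item covers operations done and operations planned. It shows that early re-operation is allowed for, not that it is common.
- A reader might infer a large loss of power. To count in f, a failure must be detected, re-operated, closed and scanned, all by 3 months, and the documents give no rate for any of these steps. At f of 5% to 10% the loss is about 2 to 5 points.
- A reader might infer that a known failure without a 3-month OCT will be dropped. The available-subjects rule permits that, but the article does not say that such a participant counts as missing.

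Two further points stand. With equal f the effect is dilution only, with no bias when positioning has no effect, and the further-surgery outcome would make rescue visible. And status at 3 months regardless of surgery is a recognisable choice that keeps the endpoint wholly masked, whereas counting re-operation as failure brings in a decision by unmasked clinicians. Intention to treat does not settle the matter. It fixes who is analysed and in which arm, and both definitions respect it.

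**Conclusion.** The point holds as a fault of definition. As worded, the primary outcome does not separate closure by the index repair from closure by a second operation before 3 months, although the protocol makes room for such operations and its aim concerns the index repair. This does not depend on how often it happens.

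The size is unknown. With equal f in both arms, power at 86 per arm runs from 85% at f = 0 through 83%, 81% and 72% to 53% at f = 50%. These figures assume the design closure rates, a two-sided 5% test and no adjustment for covariates or site. If f differs by arm, which unmasked care makes possible, the comparison could also be biased, in a direction that the documents do not settle. Nothing here faults the stated 86 or 96 per arm.

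**What to change.** Redefine primary success as both of the following: closed on the masked 3-month OCT, and no further surgery for the macular hole in the study eye since the index operation. Count a re-operated eye as not closed even if its 3-month OCT is missing. Fix this before any comparison by arm.

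The downside is that the decision to re-operate is made by clinicians who know the allocation. To limit it, have the same masked readers grade the last OCT before re-operation where one exists, and report closure on the 3-month OCT regardless of further surgery as a sensitivity analysis.

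The cost is a sentence in the outcome definition, matched in the analysis plan. Table 1 already asks about re-operation; its date and any scan taken before it would have to be collected as well. The design rates stay at 80% and 95%, so the sample size is unchanged. The change concerns classification only and does not touch when or whether anyone is re-operated.
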